#### Control arm

Providers in the control arm offer enhanced care as usual (CAU). Usual care means that provides will operate as they currently do, without a structured approach to collaboration between CAPs and PHCPs. However, the care provided by the healers is enhanced through interactive training workshops (see Table 1). For the CAPs, the training consisted of (1) discussion about their understanding of the concept of psychosis and the information about the medical nature of psychosis, including symptoms and course of illness; (2) a review of the conventional and complimentary approaches to the care of persons with psychosis; (3) identification of potentially harmful treatment practices and possible ways to avoid their use; and (4) basic concepts of human rights. For the PHCPs, the training consisted of (1) a review of the diagnosis of psychosis; (2) evidence-based management of psychosis, using the mhGAP-IG; and (3) the roles of the different levels of the mental health system in the care of persons with psychosis. While the training of the CAPs was over 2 days, that of the PHCPs was over 1 day. The goal of the trainings was to improve the care of persons with psychosis by both groups of providers in the context of current practice in which formal collaboration does not occur.

### Responses to harmful treatment practices

COSIMPO is designed to engender collaboration between CAPs and PHCPs to enhance the outcome of patients with psychosis. CAPs, in the course of delivering care to persons with severe mental health disorders, including psychotic disorders, may use what can be regarded as potentially harmful or abusive approaches. These approaches are largely informed by their understanding of the nature of psychosis by CAPs and by the need to curtail difficult clinical situations. For example, CAPs might believe that patients who are aggressive are possessed of evil spirits and that physically beating such patients might drive out the spirits. Also, in handling patients who are violent and at risk of harm to self or to others, CAPs might feel the need to shackle such patients to restrict their movements and the attendant risk of violence. All of these possible scenarios that might lead to the use of harmful or abusive practices are addressed within COSIMPO through training of the providers, as described in this protocol, and through the implementation of the collaboration with PHCPs who are able to administer medications to calm agitated and potentially violent patients.

There is need to reduce risks to all the TPs (in both intervention and control arms) as much as possible while getting the scientific and socially valuable information the study has potential to offer. To this end, a schedule of responses to harmful practices is developed to guide the research team to ensure that the team is not complicit to the use of harmful practices by CAPs while at the same time keeping the CAPs sufficiently engaged in the study in order to answer the study questions. The schedule sets out a typology of responses to some of the more common forms of harmful practices that may occur in either arm of the study. Responses are determined by the severity of the practice (see Table 2). CAPs who engage in harmful practices are expected to cooperate with the research team in the execution of the responses to these practices and to reduce such practices.

**Table 2 Tab2:** Schedule of response to harmful practices

Practice observed	Thresholds of harm	Responses control arm	Responses intervention arm
Shackling	1. Short-term (hours) 2. Infections due to long-term shackling	1. Continued monitoring 2. Study team works with CAP to treat infections (by facilitating access to medical care)	1. PHCP consultation and study team consultation to employ alternative measures 2. PHCP will treat the infection; if more medical or specialist care is required, PHCP will initiate referral to such care
Beating	1. Evidence of beating – equipment for beating present at site 2. Evidence of beating particular patient (marks, scars)	1. Continued monitoring 2. Continued monitoring	1. PHCP consultation and study team consultation not to beat patients 2. PHCP to reinforce the need to avoid practice
Scarification	1. Wounds have healed 2. Wounds are yet to heal	1. Continued monitoring 2. Study team works with CAP to treat infections(by facilitating referral to hospital)	1. PHCP to reinforce the need to avoid practice 2. PHCP will treat infection and reinforce the need to avoid practice (and if necessary, initiate referral to medical care)
Herbs	1. Patient shows non- serious signs of side effects or drug reaction (e.g., vomiting, skin rash, etc.) 2. Patient is seriously unwell as a reaction to herbs	1. Continued monitoring 2. Work with CAP to treat illness (by facilitating referral to hospital)	1. PHCP monitors the situation and offers suggestions about avoiding herbs 2. PHCP will assess and treat the condition; if more medical or specialist care is required, PHCP and study team will facilitate access to such care
Sexual abuse	1. Any report or other evidence of sexual abuse	1. Study team reports to legal authorities	1. Study team reports to legal authorities

*CAP* complementary alternative health provider*,PHCP* primary health care provider

Disengagement of a CAP from the study will occur at a defined instance of continued refusal to cooperate with the study team in implementing these harm-reduction responses. Given that harmful practices are often a part of the standard of care of some CAPs and are among what the project sets out to change, direct intervention by the research team will be determined by the need to ensure that the patient’s safety is promoted while ensuring that the scientific objectives of the study are accomplished. The decision about when and how the research team will take action or intervene with patients and/or caregivers to ensure the protection of the patients against the consequences of harmful practices is be guided by specific rules. These rules are set out to enhance patient safety while giving sufficient scope for the trial to meet its scientific objectives.

Thus, the PHCP will respond to harmful practices in the intervention arm by providing appropriate treatment to the patient and facilitating hospital referral when necessary. PHCPs will also directly intervene with the patients and their caregivers by providing advice on seeking alternative treatment in instances of CAPs refusing to cooperate in the management of a case of life threatening or “severe” harmful practice or when such practice has been observed on more than two occasions at a particular CAP facility. In the control arm, where PHCPs are not involved, the trial team will perform the role of engagement with patients and caregivers using the decision rules described in Table 2.

Information on observed harmful practices will be documented by the RAs and the PHCPs in a form designed for the purpose to track the type of harmful practice, the rating of its severity, the immediate response of the PHCP or RA to the observed practice, the outcome and planned follow-up action.

### Outcome evaluation

Outcome measures will be undertaken at 3 and 6 months by RAs.

*Primary outcome*, to be assessed at 6 months, will be the mean difference in recovery rate from psychosis as measured by improvement or reduction in mean PANSS total scores of patients in intervention arm (from baseline) compared to those in the CAU arm. The PANSS is chosen for its demonstrated acceptability and validity, its proven sensitivity to change and our experience with its use in our previous and on-going studies in Nigeria.

*Secondary outcomes*, to be assessed at 3 and 6 months, include levels of disability, of self-stigma, the experience of harmful treatment practices and of victimization by caregiver as well as the course of the psychotic illness in four key domains (symptoms, treatment, residence and work.

### Assessment instruments

The psychosis section of the Structured Clinical Interview for DSM-IV Axis 1 disorders (SCID) is used to confirm the diagnosis of psychosis. The SCID is a semi-structured interview for making the major DSM-IV Axis 1 diagnosis. Information collected by trained RAs using the SCID is reviewed by research psychiatrists to assign subtype diagnosis of psychosis and make a rating on course of the psychosis illness. The Positive and Negative Syndrome Scale (PANSS) [28] is used to measure symptom severity of psychosis at baseline, 3 and 6 months. Disability is being measured with the World Health Organization’s Disability Assessment Schedule 2.0, a generic tool for assessing health and disability [31]. The Proxy version of WHO-DAS is used when a TP is unable to provide reliable information. The 29-item Internalized Stigma of Mental Illness (ISMI) scale [32] is used to assess level of self-stigma. The burden of caring for TPs by their caregivers is being assessed with the Family Burden Interview Schedule (FBIS) [33], a standardized instrument designed for the. The Life Chart Schedule (LCS) is being used to assess the long-term course of the psychotic illness in four key domains (symptoms, treatment, residence and work) [34]. To capture the range of services and the cost associate with their use, we use the Service Utilization Questionnaire [35] (adapted for COSIMPO). The SUQ systematically collects resource-use data, including cost of care received from CAPs, consultations with PHCPs and with other conventional health providers, use of herbs and drugs, cost of treatment, including those of rituals and sacrifices, and any other service use-related costs. Checklists of harmful treatment practices, human rights’ abuses and of victimization, developed with information obtained during the formative stages of the Partnership for Mental Health Development in sub-Saharan Africa (PaM-D), are used for the indicated purposes. These assessments are conducted through both observation during visits by the RAs to CAPs facilities and by patient interviews. For example, respondents are asked if they have experienced any of the practices or abuses in a defined period of time (at the baseline, this will be in the previous 3 months, and at follow-up assessments, this will be “since the last time we spoke with you”). Every positive answer is followed by exploration of the number of times that the event had been experienced or the duration of its occurrence, whichever is relevant to the event.

In order to assess the extent to which collaboration affects the knowledge and attitude of the CAPs, we administer the Knowledge About Schizophrenia Interview (KASI) [36], a semi-structured interview that enquires about respondent’s view about the diagnosis, symptomatology, etiology, course, prognosis and management of schizophrenia, to the CAPs participating in the study at the baseline and at the 6-month primary endpoint.

### Discontinuation criteria

Trial participants will be discontinued from the trial at any point in the following instances:Development of a life-threatening physical illness in which a referral to hospital is strongly advisedSerious suicidal intent (indicated by a suicidal plan or attempt)Becoming pregnant (confirmed by a detailed history of menstruation and a urine test)Incarceration

Patients, who during the routine weekly visit by the research team or by the PHCP, are reported or observed to meet any of these criteria, will be assessed immediately by the trial manager on whose recommendation the site leader will decide on possible discontinuation. The data collected on any patient who discontinues from the study will be retained in the study up to the time of the discontinuation and included in the analysis on an intent-to-treat basis.

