### Outcome analyses

The primary analyses will be intention-to-treat at the 6-month follow-up visit adjusted for baseline measures. That is, after randomization, patients will be analyzed according to their allocated treatment irrespective of the treatment that they actually received. These analyses will also disregard adherence to the intervention or withdrawal from the trial. Random-effects logistic regression will be used to analyze binary outcomes, adjusting for country site and cluster size as random-effects variables. Analyses of continuous outcomes will use random-effects linear regression, additionally adjusting for the baseline value of that outcome. Adjustments will also be made for any a-priori-defined sets of potential confounding variables for which randomization did not achieve balance between the two arms at baseline. This may include, for example, differences in the type of CAPs (e.g., traditional healers versus faith healers). Effect sizes will be reported as: (1) crude and adjusted relative risks (ARRs) estimated using the marginal standardization technique with 95% confidence intervals for the ratios estimated via the delta method [46] for binary outcomes and (2) as mean differences and standardized mean differences (SMDs), with 95% confidence intervals for continuous outcomes. Missing data on the outcomes will be estimated using multiple imputations in Stata. Secondary analyses will include repeated measures analyses of data collected at 3 and 6 months, which make efficient use of all available data. No interim analysis of outcomes is planned.

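### Participants discontinued from the trial before month 6 have no observed primary outcome, because the discontinuation rule ends data collection as well as participation

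*Protocol article*

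**What the plan says.** The Discontinuation criteria section opens with "Trial participants will be discontinued from the trial at any point in the following instances" and lists life-threatening physical illness for which hospital referral is strongly advised, serious suicidal intent, pregnancy and incarceration. Removal is not automatic. Patients "who during the routine weekly visit by the research team or by the PHCP, are reported or observed to meet any of these criteria" go to the trial manager for assessment, and the site leader then decides. Data on those who leave "will be retained in the study up to the time of the discontinuation and included in the analysis on an intent-to-treat basis".

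Under Outcome evaluation, the primary outcome is set at 6 months and "will be the mean difference in recovery rate from psychosis as measured by improvement or reduction in mean PANSS total scores". Under Outcome analyses, "The primary analyses will be intention-to-treat at the 6-month follow-up visit adjusted for baseline measures". That section defines intention-to-treat as analysis by allocated arm, adds that "These analyses will also disregard adherence to the intervention or withdrawal from the trial", and then states that "Missing data on the outcomes will be estimated using multiple imputations in Stata".

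PANSS is measured at baseline, 3 and 6 months (Assessment instruments). The 6-month assessors are a separate group, kept blind to allocation (Blinding).

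**The concern.** The rule takes a participant out of the trial, not only out of the intervention, and stops the data at that date. A participant discontinued in month 2 has a baseline PANSS only. One discontinued in month 4 has baseline and 3-month scores. Neither has the 6-month score on which the primary comparison rests.

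Some of the criteria are plausibly linked to that score. Serious suicidal intent, and perhaps life-threatening illness, may accompany a worsening of the psychosis. If the worsening follows the last PANSS and is the reason for leaving, nothing recorded on that patient's PANSS shows it.

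The share who leave could also differ by arm. Scheduled weekly visits by primary care providers belong to the intervention (Intervention arm), and the section on responses to harmful practices says these providers are not involved in the control arm. They are therefore an additional reporting route in one arm, on top of research-team visits. At stake is a bias in the primary PANSS difference that a later analysis plan could explore but not remove, because the scores would never have been sought.

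**Working it through.** **The plan's own figures.** The protocol gives no discontinuation rate, only 20% total attrition not split by reason. The inputs used to judge size come from the sample size section: difference 7.5, SD 20, power 80%, alpha 0.05, six patients per cluster, ICC 0.02.

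- Per arm: 2 × (1.96 + 0.84)² × 20² / 7.5² = 111.5, rounded up to 112, as stated.
- Design effect: 1 + (6 − 1) × 0.02 = 1.10, and 224 × 1.10 = 246.4, as stated.
- With the plan's 20% addition: 246.4 × 1.20 = 295.7, rounded up to 296, as stated.

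**Is there an observed 6-month PANSS after discontinuation?** Reading the sections together: removal is from the trial; data are kept to that date; the schedule sections add no exception; the analysis section supplies a method for missing outcomes. The 6-month value is therefore imputed, not observed.

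**Formula for the bias.** Let p be the share of an arm discontinued before month 6, and g the number of PANSS points by which their true 6-month score is worse than the imputed one, taken as the same in both arms. Each arm's mean is then understated by p × g, so the control-minus-intervention difference is understated by

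(p control − p intervention) × g.

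The rates and gaps below are assumptions; the protocol gives none.

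| Intervention | Control | g = 10 | g = 20 | Share of 7.5 |
|---|---|---|---|---|
| 5% | 5% | 0 | 0 | 0% |
| 2% | 5% | 0.3 | 0.6 | 4% to 8% |
| 5% | 10% | 0.5 | 1.0 | 7% to 13% |
| 2% | 10% | 0.8 | 1.6 | 11% to 21% |
| 10% | 5% | −0.5 | −1.0 | −7% to −13% |

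Positive values mean that the benefit is understated, negative values that it is overstated. Exchanging the arms changes only the sign. Equal rates give zero only if the gaps are also equal: 5% in each arm with gaps of 20 and 10 gives 0.05 × (20 − 10) = 0.5.

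**Against sampling error.** Keeping 80% of 296 leaves 236.8, or 118.4 per arm. The standard error of the difference is √(2 × 20² × 1.10 / 118.4) = 2.7 points, before any gain from baseline adjustment. The largest tabulated bias is 1.6 / 2.7 = 0.6 standard errors; most of the table is below 0.4.

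**Patients affected.** Of 296, the assumed 2% to 10% is about 6 to 30 people.

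**The case against.** The strongest reply is that the analysis section is coherent as written. Disregarding withdrawal means that leaving the trial does not take a patient out of the allocated arm, and multiple imputation then supplies the outcome. A reader might infer that the sections contradict each other, or that the intention-to-treat analysis is impossible. The text does not support that.

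Other strong readings also go too far:

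- *Discontinued patients receive values typical of those who did well enough to stay.* No imputation model is given, and specifying one can be left to the analysis plan. It may condition on the patient's own baseline and 3-month scores. Only the part those scores do not explain is at risk.
- *The most harmed patients vanish from the harmful-practice and disability comparisons.* Data before discontinuation are kept, missing outcomes are to be imputed, and observed harmful practices are recorded by research assistants and primary care providers.
- *Only the intervention arm has weekly detection.* The rule also names research-team visits and does not limit them to one arm. Every case goes through the same assessment and decision.
- *A serious herb reaction leads to discontinuation.* Table 2 gives treatment or referral for it. The link to discontinuation is an inference.
- *Everyone who meets a criterion leaves.* The site leader decides on possible discontinuation. Pregnancy, moreover, has no evident link to PANSS.

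It is also fair that the size rests wholly on assumed rates, that opposing mechanisms may partly cancel, and that the full protocol may say more. What stands is that the article states a rule on data collection, and that rule ends collection at discontinuation. An analysis plan cannot restore scores that were not sought.

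**Conclusion.** The point holds in a limited form. As stated, the rule leaves every participant discontinued before month 6 without an observed primary outcome, and for serious suicidal intent, at least, the loss may be related to that outcome. Imputation retains these patients but cannot recover a deterioration after the last assessment.

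The direction of any bias is unknown. More events in the control arm would tend to understate the benefit; more reporting in the intervention arm would tend to overstate it. Under assumed rates of 2% to 10% and a common gap of 10 to 20 points, the size is 0 to 1.6 PANSS points, and zero if rates and gaps are equal. This does not invalidate the primary analysis. It is an avoidable loss of primary-outcome data that can be reduced cheaply.

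**What to change.** In the Discontinuation criteria section, separate stopping the trial intervention from stopping follow-up. Suggested text:

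*For participants who meet a discontinuation criterion, the 3- and 6-month assessments, with the PANSS first, will still be sought by the usual assessors unless consent is withdrawn. The results will be analysed in the allocated arm.*

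Report discontinuations by arm and by reason. For those still without a 6-month PANSS, a delta-adjusted sensitivity analysis, in which imputed scores are worsened by a range of amounts separately by arm, is a useful addition and can sit in the statistical analysis plan.

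The cost is a wording change and a few extra visits by assessors already in place. Some of these participants, such as those in hospital or custody, will be harder to reach. If continued follow-up was already intended, the added text settles the matter. The change concerns data collection only; the clinical criteria and the decision process stay as they are.

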### Blinding

TPs are not blinded to their treatment arms (as it is impossible to conceal the fact of collaboration or lack of it from the patients). There are two groups of trained assessors: the RAs who conduct the baseline and 3-month assessments, and those conducting the 6-month primary outcome evaluations. While the former cannot be blind to patient trial arm (since they will conduct the baseline assessment at the recruitment facility and the TP may still be on admission at that facility for the 3-month outcome assessment), the latter will be kept blind to trial allocations. TPs will be instructed not to disclose whether or not they are receiving the intervention to the primary outcome assessors. The primary outcome measure (PANSS) will always be completed first in order to minimize the risk of bias in the event of unmasking during the assessments and, if it occurs, the point of unmasking will be recorded. Sensitivity analyses will be carried out to assess the effect of unmasking on the primary outcomes.

### Data collection and quality control

Data collection and capture are regulated by a series of specific steps described in the Data Management Protocol. The protocol specifies steps to be taken to ensure data integrity and quality.

Data is being collected using pen and paper. Collected data is checked for accuracy and consistency by the RA, the supervisor, the trial manager and the data-entry clerk before it is entered using the Mobenzi software. Mobenzi obeys series of programmed instructions such as “Skip patterns” and thus ensures seamless data entry and quality. At the end of every entered interview, Mobenzi prompts a message pop-up to request the acceptance or rejection of the case.

Field work is monitored by research supervisors to ensure that assessments are conducted according to protocol specifications. Supervisors make random checks on the quality of interviews (by physically observing at least 10% of all interviews conducted by an RA) and randomly check the correct entry of study data by RAs. The supervisors work under the direction of the trial manager. The supervisors provide first-line response to research and clinical issues as they arise in the field and consult or refer difficult issues to the site trial manager. Any unanticipated problem encountered by an RA is reported to the supervisor who is required to either solve the problem or report the problem to the trial manager. Problems that cannot be solved by the trial manager are referred to the site leader or the principal investigator (PI).

The trial managers at both sites are responsible for the coordination of the field work and are responsible to the Trial Management Team through the site leader (in Ghana) or the PI (in Ibadan). The trial manager at each site ensures protocol adherence and monitors the work of the RAs and research supervisors.

